## Abstract

**Background:**

Multisensory interactive training has an increasingly prominent role in stroke rehabilitation. Currently, there is insufficient evidence to demonstrate its efficacy on gait improvement, upper limb and lower limb functional improvement, global motor function and cognitive improvement. A recent Cochrane review confirmed that published studies on virtual reality (VR) training have the limitations of lack of powered sample size, did not evaluate the benefits over a long-term period and lacked trial quality on cognitive function. Another systematic review also concluded that the evidence for the use of VR in gait and balance improvement is limited. This study investigates the effects of multisensory training on gait pattern, upper and lower limb biomechanics, upper limb gross and fine motor functions, and lower limb functional recovery over a medium- to long-term period.

**Methods:**

Two hundred and twenty-four acute stroke patients will be recruited from a single centre over a period of 6 years. Participants will be randomly assigned to either conventional therapy or conventional therapy with VR training. Outcomes will be recorded at baseline, post intervention and at 3, 6 and 12 months post intervention. Primary outcome measure is gait speed. Secondary outcome measures include kinematic data of upper and lower limb motion, muscle tone, Action Research Arm Test and Short Orientation Memory Concentration Test.

**Discussion:**

The results of this trial will provide in-depth understanding of the effect of early VR interventions on gait, upper and lower limb biomechanics and how it may relate to changes in functional outcomes and muscle tone.

**Trial registration:**

Chinese Clinical Trial Registry (Registration No.: ChiCTR-IOC-15006064). Registered on 11 May 2015.

**Electronic supplementary material:**

The online version of this article (doi:10.1186/s13063-017-1874-y) contains supplementary material, which is available to authorized users.

## Background

Stroke is the third leading cause of disability worldwide [1, 2]. Stroke survivors often have an abnormal hemiparetic gait pattern that is characterised by decreased gait speed [3], altered kinematics of hip, knee and ankle joints during a gait cycle [4] and functional impairment of lower and upper extremities. Impaired ability to walk is one of the most devastating consequences and gait recovery is often regarded as a primary objective in stroke rehabilitation [5]. It is becoming widely recognised that multisensory VR training is an important component of stroke rehabilitation and one that has demonstrated potential to promote gait, lower and upper limb functional recovery, and thus increase quality of life.

Virtual reality (VR) has been subjected to intense research over the past decade as an intervention to promote functional recovery for patients with stroke. The virtual environment offers multisensory interaction and goal-orientated tasks that can stimulate active repetitive movements and offer instant feedback [6]. VR is relatively low cost and may be employed within home settings where patients live remotely or have other barriers to participate in intervention [7]. The concept of using commercial gaming (CG) systems to deliver VR interventions at home as part of the rehabilitation programme was well received among stroke survivors as they believed it to be beneficial for functional recovery [8]. Previous studies on VR interventions indicated that they may be more effective in improving gait, lower limb functions [9, 10] and upper limb functions [11] when compared to conventional therapy. Functional imaging studies have indicated that cortical reorganisation is associated with gait improvement post-VR interventions. The latest published meta-analysis [7] suggested that VR interventions are at least as effective as conventional physiotherapy in improving lower limb outcomes within the stroke population.

Gait performance is a predictor for disability [12, 13], mortality and morbidity [14]. Early intervention with physical therapy to restore gait function had been shown to improve motor function and decrease the subsequent disability when compared to intervention provided at the subacute or chronic stages [15]. Despite the reported positive results for VR interventions, published systematic reviews concluded that the evidence for VR in gait, lower limb functions and balance improvement is limited [16], particularly for stroke patients during the acute stage [17]. It was argued that since most of the neuroplasticity activity took place within the first month of stroke occurrence, VR intervention provided during the acute stage of stroke is likely to lead to better clinical outcomes for gait and lower limb functions [18]. A Cochrane review [19] also concluded that there was insufficient evidence to demonstrate the efficacy of VR training on gait speed and global motor function improvement due to a lack of powered sample size and did not evaluate the effectiveness of VR over a long-term period or post hospital discharge. Thus, little is currently known about the impact of VR on gait and lower limb functions during the acute stage and if the impact is sustainable in the long term.

The recovery of upper limb function to perform delicate motions, such as grasping, finger pinching and individual finger movement continues to be a challenge for stroke survivors [11]. Existing rehabilitation programmes, such as constrain-induced therapy, imagery training and bilateral training, have focussed on the improvement of upper limb gross motor skills [20–22]. These training regimes have insufficient emphasis on fine motor skills and coordination of limb movements; thus, leading to reduced ability to carry out activities of daily living. Sophisticated robotic devices have been developed to provide the possibility to train hand and finger motor skills [11]. However, these types of devices are not easily accessible in most rehabilitation departments. In addition, fine motor movement involves the combination of cognitive and motor functions to plan and execute it. Cognitive function refers to the ability to process received information, and to take appropriate action accordingly [12]. Large numbers of stroke survivors have cognitive impairment which presents an additional challenge in upper limb functional recovery. Previous studies have indicated that cognitive function can be recovered through repetitious training [13]. Two Cochrane reviews [19, 23] suggest that VR interventions appear to be promising with moderate-quality evidence to support the beneficial effects on upper limb functional improvement. However, the number of studies available are too few and too small to draw conclusions on upper limb recovery and cognitive function improvements induced by VR interventions. In addition, most of the studies assessed gross motor function by functional outcome measures such as the Action Research Arm Test and the Fugl-Meyer Assessment of Motor Recovery. While they are validated clinical tests, several authors cast doubts on the use of functional outcomes to study motor recovery post stroke. It was argued that functional outcome measures only focussed on task accomplishment regardless of the quality of movement [24, 25]. Since motor compensation can affect [26, 27] task accomplishment, it is, therefore, essential to understand the impact of VR on motor performance measures and to cross reference with functional outcome measures.

## Hypotheses

The primary aim of this study is to test the hypotheses that patients with stroke who receive VR training during the acute stage will have significantly higher improvement in gait speed, lower limb motor functions and upper limb gross and fine motor functions when compared to those who receive conventional therapy. The observed improvements in the VR group will remain significantly higher than the conventional therapy group at 3-, 6- and 12-month follow-up periods. The secondary aim of this study is to assess the changes of the kinematic characteristics of gait and upper limb motions of ‘reach forward’ and ‘reach forward and grasp’ after 3 weeks of VR interventions and at 3-, 6- and 12-month follow-up periods.

## Methods

### Study design

This study is a single-blind randomised controlled trial (RCT) to compare the differences between two parallel groups.

### Study setting

This is a single-centre study which will be conducted by the Rehabilitation Department of the Sun Yat-sen University, China. Participants will be recruited from the inpatient ward. All interventions will be delivered within the Hospital Rehabilitation Department by hospital staff.

### Recruitment

Patients who are admitted to the inpatient ward will be screened for eligibility as part of routine assessment. Suitable participants will be identified by the clinical team and given written information about the study. They will then be approached by a member of the research team to inquire whether they are interested and willing to take part in the study. Written consent will be obtained from participants who are willing to participate. A screening log of all nonrecruited patients and reasons for exclusion will be maintained.

### Randomisation

Participants will be randomly allocated to the control or VR groups. A randomisation schedule will be pre-generated by the permuted block randomisation technique, using blocks of 10 participants with a 1:1 allocation ratio. The randomisation schedule will be calculated in SPSS by a statistical expert from the Faculty of Medical Statistics and Epidemiology, Sun Yat-sen University. The sequences of allocation are kept in a sealed envelope. The randomisation process will allocate each participant an identification number, which will appear on all report forms to maintain confidentiality.

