### Intervention group

The intervention group will participate in a multisensory VR training programme for 5 days a week for 3 weeks. VR training is provided in addition to the routine programme. It consists of four components: gait training, limb coordination, gross motor function and fine motor function.

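### A fixed, published block size of 10 in a single-centre trial with visible treatments leaves about one allocation in six knowable to anyone who counts

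*Protocol article*

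**What the plan says.** All references are to the protocol article.

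- **Randomisation.** "A randomisation schedule will be pre-generated by the permuted block randomisation technique", "using blocks of 10 participants with a 1:1 allocation ratio". No stratification factor and no variation in block size are stated. A statistical expert in a separate university faculty produces the schedule. On concealment the text says: "The sequences of allocation are kept in a sealed envelope".
- **Study setting.** "This is a single-centre study which will be conducted by the Rehabilitation Department", and "All interventions will be delivered within the Hospital Rehabilitation Department by hospital staff".
- **Study design and Intervention group.** "This study is a single-blind randomised controlled trial (RCT) to compare the differences between two parallel groups". The article does not say who is blinded. "VR training is provided in addition to the routine programme", and no sham is described for the control group.
- **Recruitment and Ethics.** "Suitable participants will be identified by the clinical team and given written information about the study". A member of the research team then makes the approach. A log of non-recruited patients with reasons is kept, and the Ethics section says that every patient who meets the criteria is invited.
- **Safety and adverse event reporting.** The therapists who deliver the sessions work closely with the inpatient clinical team.
- **Data analysis.** Pre-to-post differences in gait speed are compared between groups by one-way ANOVA. No covariates are named.

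**The concern.** With a constant block size that everyone can read, the end of each block can be worked out by counting. Counting needs three things, and the article supplies or allows all of them. There is one sequence at one site. The allocations are visible, because a patient either trains on the VR equipment or does not. And there is a route from those who see allocations to those who identify the next candidates. Blinded outcome assessment, if that is what single-blind means here, would not prevent prediction at the point of enrolment.

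What is at stake is comparability of the arms. A patient may enter at any time within 1 month of stroke, and medical stability and walking with or without assistance call for judgement. An approach could therefore be brought forward or delayed within the rules. If the next arm is known, patients expected to recover faster could drift into one arm. That would bias the between-group difference in gait-speed change in a way that the planned analysis would not detect.

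**Working it through.** **Inputs.** Block size 10, ratio 1:1 (so 5 + 5), one sequence, one centre (Randomisation; Study setting). Total 224 (Sample size). The article gives no predictability figure of its own to reproduce. The total of 224 enters only as a multiplier.

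**Assumption.** The guesser sees every past allocation, knows where the sequence starts, and influences enrolment. The results are therefore a ceiling.

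**Step 1: allocations known with certainty.** The last k slots of a 5 + 5 block are all known once one arm has used its five places, that is, when those k slots all belong to the same arm:

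P(last k known) = 2 × C(10 − k, 5) / C(10, 5), with C(10, 5) = 252.

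- k = 1: 2 × 126/252 = 1.000
- k = 2: 2 × 56/252 = 0.444
- k = 3: 2 × 21/252 = 0.167
- k = 4: 2 × 6/252 = 0.048
- k = 5: 2 × 1/252 = 0.008

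The expected number known is the sum, 1.667 per block, or 16.7%. In 224 patients there are 22 full blocks and 4 patients over. 22 × 1.667 = 36.7. The last 4 add none, because certainty needs five patients already in one arm. So about 37 of 224 are certain (36.7/224 = 16.4%).

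**Step 2: best-guess rate.** Always guessing the arm with more places left gives, for half-block m = 5:

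expected correct = m + 2^(2m − 1)/C(2m, m) − 1/2 = 5 + 512/252 − 0.5 = 6.53 of 10, or 65.3%.

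Over 22 blocks this is 143.7 of 220, against 110 by chance. An exact recursion over the places left in the block gives the same 6.53 and 1.667.

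**Step 3: what varied blocks would do.** The article names no alternative, so the sizes below are assumptions. Sequences of 224 were simulated (1,000 runs, each size equally likely). The guesser updates by Bayes' rule and knows the set of sizes but not the current one.

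| Block sizes | Known with certainty | Best guess correct |
|---|---|---|
| Fixed 10 | 16.4% | 65.1% |
| 4, 6 | 5.5% | 69.3% |
| 4, 6, 8 | 2.4% | 68.1% |
| 6, 8, 10 | 1.5% | 66.4% |

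With 6, 8 and 10 the expected number of certain allocations is about 0.015 × 224 ≈ 3, against about 37. The best-guess rate does not fall. Small blocks raise it, so they should be avoided.

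**The case against.** The strongest case for the plan is that a fixed block of 10 is a common choice and contradicts nothing in the article. It is less predictable than a smaller fixed block: at size 4, 33% of allocations are certain and 71% can be guessed. Roles are partly separated, since a statistical expert in another faculty generates the list, a research team member makes the approach, and a dedicated team assesses outcomes. The log and the rule to invite all eligible patients limit selective enrolment and would help to expose it. Nothing says that the person taking consent keeps a running count.

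All of this stands, and it makes the weakness a modest one. It does not remove it. The log and the rule govern who is approached, not when, and the article itself describes close contact between the treating therapists and the inpatient clinical team.

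Three stronger readings are tempting but not supported:

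- A reader might infer that one sealed envelope holds the whole list, so that opening it exposes every later allocation. The sentence is condensed article text. It does not say that there is a single envelope for the list, who holds it, or how it is opened. Those details may sit in the full protocol.
- A reader might infer that the primary test ignores baseline. The ANOVA is on pre-to-post differences, so baseline speed is already subtracted. What it cannot remove is selection on expected recovery, which acts on the change itself.
- A reader might object that 224 is not a multiple of 10, so the arms could end at 110 and 114. That needs the last four patients all in one arm, with probability 12/252 = 4.8%. An exact 112/112 split has probability 120/252 = 48%. The difference is immaterial either way.

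**Conclusion.** The point holds as a modest design weakness that is worth correcting while recruitment continues. The fixed and disclosed block size lets a person with full sight of past allocations know about 16.7% of allocations outright (about 37 of 224) and guess about 65% correctly. Both figures are upper bounds that assume perfect tracking by someone able to influence enrolment.

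Two things are inferred rather than stated: that delivering staff know the arm (unavoidable with added VR and no sham), and that this knowledge could reach those who identify candidates (plausible from the described contact). A reader might go further and conclude that the arms are already biased. The article gives no evidence of that, and no effect on gait speed can be calculated from it.

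**What to change.** For patients still to be randomised, the statistics faculty that already generates the schedule should issue a new list with randomly varying block sizes that are not small, for example 6, 8 and 10. The sizes should be withheld from the site and from publication until enrolment ends. The faculty should also confirm in writing that each allocation is released one at a time, after consent and baseline assessment. If that is already the procedure, one sentence in the protocol settles it.

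This is feasible: recruitment has run since May 2015 and is planned over 6 years.

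**Cost.** One new list and a short procedure note. Treatments, outcomes and sample size do not change.

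**Downside.** The gain is almost entirely in removing certain allocations. If the set of sizes becomes known, the best-guess rate stays at about 66%, marginally above the present 65%, so non-disclosure matters. An unfinished last block can leave a final imbalance of at most 5 patients (half of a block of 10), which is trivial in a trial of 224.

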### Sample population

This study has the following inclusion criteria: (1) within 1 month of the first occurrence of stroke, (2) stage 2 of the Brunnstrom classification, (3) magnetic resonance imaging (MRI)- or computed tomography (CT)-confirmed stroke, (4) age between 40 and 80 years, (5) have at least 20° of wrist flexion/extension and at least 10° of finger flexion and extension of the affected limbs, (6) be able to walk at least 10 m with or without assistance and (7) no severe cognitive impairment (Mini Mental State Examination score below 10 [28]).

This study will exclude participants who are: (1) medically unstable, (2) have already received elements of the training programme over 1 week and (3) have brain stem injury.

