## Data analysis

Descriptive statistics will be used to describe the demographic data of each sample group. The normality of each parameter will be checked by histogram and the Kolmogorov-Smirnov test.

Chi-squared tests will be used to assess sample characteristics of gender and types of cerebral infarction.

The pre- and post-intervention differences in gait speed within individuals and between groups will be assessed by paired-samples *t* tests (two-tailed) and one-way analysis of variance (ANOVA), respectively. The comparison of 3-month, 6-month and 1-year follow-ups will be assessed by repeated-measures ANOVA.

A broadly similar approach will be used to analyse the secondary outcome measures of muscle tone, other kinematic parameters of gait, reach forward motion and reach forward and grasp motion. The kinematic parameters of the paretic side will be compared with the nonparetic side at all recording points using paired-samples *t* tests.

The Mann-Whitney *U* test will be used to test the between-group differences for the ordinal data obtained from the functional outcome measures and WHODAS 2.0.

The differences between the two groups during the follow-up phase will be assessed by the Kaplan-Meier test.

There are no planned interim analyses or stopping rules, as the power calculation has accounted for loss to follow-up. All analyses will initially be performed on an intention-to-treat basis.

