## Discussion

The VR intervention works on the principle of neuroplasticity [31]. Studies from the past decade suggest that different types of VR can increase gait speed, lower and upper limb functions and kinematic parameters. There are a number of clinical guidelines which recommend active rehabilitation to be commenced within 24 to 48 h of stroke occurrence [32, 33] as the greatest part of the recovery was reported to take place in the first month following stroke [34]. There is some evidence to demonstrate the benefit of an early exercise programme on functional recovery but evidence for early VR intervention is lacking. The majority of the published studies focussed on patients with subacute and chronic stroke [16, 23]. Thus, this study will provide evidence for the use of VR as part of an early intervention programme.

The present study also assesses the medium- to long-term impact of VR interventions for patients with stroke during the acute stage. The Cochrane reviews published in 2011 and 2015 [6, 19] both concluded that it was unknown whether the effects of VR were sustained in the longer term. The review [35] found that only one study [36] out of the 37 included studies had measured the effects of VR on upper limb functions at the 6-month follow-up. Motor capacities evolve most strongly over the first month post stroke [37] and intervention provided at an early stage has better clinical outcomes when compared to intervention provided at a later stage of stroke. Thus, the follow-up data record at 3, 6 and 12 months post intervention will increase the understanding of whether early VR intervention is superior to conventional therapy in the longer term.

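### Patients enter at any time up to 1 month after stroke, when the protocol says recovery is steepest, but the gait-speed comparison is unadjusted for time since onset: a valid test that gives up precision, beside a hypothesis worded more tightly than entry ensures

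*Protocol article*

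**What the plan says.** Protocol article, Sample population: the only limit on time since stroke is inclusion criterion (1), "within 1 month of the first occurrence of stroke". No lower limit is given, though patients must also be medically stable, at Brunnstrom stage 2, and "be able to walk at least 10 m with or without assistance".

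The article treats this month as special in three places. Background: "most of the neuroplasticity activity took place within the first month of stroke occurrence". Discussion: "the greatest part of the recovery was reported to take place in the first month following stroke" and "Motor capacities evolve most strongly over the first month post stroke".

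Hypotheses: the trial is to test whether "patients with stroke who receive VR training during the acute stage will have significantly higher improvement in gait speed". Intervention group: "The intervention group will participate in a multisensory VR training programme for 5 days a week for 3 weeks". No sentence says when training must end relative to the stroke.

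Randomisation: permuted blocks of 10, 1:1, with no stratification factor named. Data analysis: change in gait speed is compared between groups by one-way ANOVA, and the follow-up visits by repeated-measures ANOVA. No covariate is named for either.

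**The concern.** On the protocol's own account, a patient entered in the first days is on a steeper part of the recovery curve than one entered in week 4. Both then contribute a change in gait speed over about 3 weeks. Part of the spread in that change therefore probably reflects when the patient entered. A one-way ANOVA leaves this spread in the error term. It also makes no correction if one arm happens to be recruited somewhat earlier after stroke than the other.

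The second strand is wording. The hypothesis speaks of training received during the acute stage, and the Background reaches the acute stage by an argument about the first month. Eligibility fixes only when a patient enters. For late entrants most of the training can fall after that month, so the hypothesis describes something that the design does not ensure.

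**Working it through.** **1. The plan's own figure.** Sample size gives 112 per group, 90% power, a difference of 0.3 m/s and 10% missing data. It gives no number for the SD or alpha, so 112 cannot be reproduced directly. I back-solved the SD, assuming two-sided alpha 0.05:

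- Evaluable per arm: 112 × 0.9 = 100.8, about 101.
- z-values: 1.960 + 1.282 = 3.242.
- SD = 0.3 × √(101/2) / 3.242 = about 0.658 m/s.
- Check with the article's formula and equal proportions: N = 3.242² × 0.658² / 0.3² × 4 = about 202; 202/0.9 = about 224, as stated.

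**2. Precision gained by adjusting.** Let R² be the share of within-arm outcome variance explained by days since onset. The documents give no value, so a range is shown. Adjustment multiplies the SD by √(1 − R²):

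- Unadjusted SE = 0.658 × √(2/101) = 0.093 m/s.
- Power = Φ(3.242/√(1 − R²) − 1.960).

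| R² (assumed) | Adjusted SE (m/s) | Power |
|---|---|---|
| 0 | 0.093 | 90.0% |
| 0.05 | 0.090 | 91.4% |
| 0.10 | 0.088 | 92.7% |
| 0.20 | 0.083 | 95.2% |

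The SD was chosen to give 90%, so it cancels from the power column. That column depends only on the planned power, alpha and R².

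**3. Chance imbalance in onset time.** If entry were uniform over days 0 to 30 (an assumption), the SD of entry day is 30/√12 = 8.66 days. The SE of the arm difference in mean entry day is 8.66 × √(2/112) = 1.16 days, so the 95% range is about ±2.3 days.

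The effect on the gait-speed contrast, for correlation r between entry day and outcome, is r × SD × (imbalance / SD of entry day). At the 95% limit with 101 per arm this is r × 0.658 × 1.96 × √(2/101) = r × 0.18 m/s. For R² of 0.05 to 0.20, r is 0.22 to 0.45, and the shift is about 0.04 to 0.08 m/s. The target is 0.3 m/s. This variation is already part of the 0.093 m/s standard error; it does not come on top of it.

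**4. Training against the first month.** Take a 30-day month, a 21-day course and training that starts on entry day t. The share of training after the month is max(0, (t + 21 − 30)/21).

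| Entry day | Share after day 30 |
|---|---|
| 9 or earlier | 0% |
| 14 | 5/21 = 24% |
| 21 | 12/21 = 57% |
| 28 | 19/21 = 90% |

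With courses of 19 to 21 days and months of 28 to 31 days, the day-28 figure runs from 84% to 100%. How many patients enter that late is not in the documents.

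**The case against.** The strongest reply is that randomisation balances onset time in expectation. The unadjusted comparison is then unbiased, and its standard error and type I error already allow for chance imbalance. That is correct. A reader might infer from the steep recovery curve that the gait-speed result is confounded or invalid; the documents do not support that.

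Second, the article is a condensed account, and a separate analysis plan may add covariates or a baseline table row for days since onset. This stands in part. The sentence "Chi-squared tests will be used to assess sample characteristics of gender and types of cerebral infarction" concerns categorical characteristics and says nothing against describing a continuous one, so nothing is made of it here. But the article does name the test for the primary outcome, and the test that it names is unadjusted. The point is about that stated choice.

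Third, a reader might infer that the protocol breaks its own rule when training runs past day 30, or that its acute-stage hypothesis is left untested. It does not go that far. Acute is never given a last day, and no text requires training to finish within the month. The Discussion describes early rehabilitation by when it begins. The benchmark gait-speed improvement in Sample size refers to the first 60 days after stroke, and entry by day 30 with prompt training ends by about day 30 + 21 = 51. What remains is a mismatch of wording.

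Fourth, the entry criteria (medical stability, walking 10 m, Brunnstrom stage 2) probably narrow the spread in recovery, so the uniform 0-to-30-day case is only an illustration. This stands, and it is a reason not to lean on any one value of R².

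**Conclusion.** The point holds as a matter of efficiency and wording. The stated one-way ANOVA is valid, but it leaves unused a baseline variable that the protocol itself describes as closely tied to recovery and that must be known to establish eligibility. If that variable explains 5% to 20% of the outcome variance, power would be about 91% to 95% instead of 90%. If it explains almost nothing, almost nothing is gained. These figures rest on two-sided alpha 0.05, about 101 evaluable patients per arm, an SD back-solved from the stated sample size, and an assumed R². The sample size does not need to change.

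On wording, entry within 1 month supports a statement about when training started. It does not support one about all training being given in the first month. For late entrants the two differ widely, by about 90% of the course for entry on day 28.

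**What to change.** - In Data analysis, replace the one-way ANOVA for gait speed with a prespecified linear model (ANCOVA) that has treatment group and days from stroke onset to randomisation, the latter as a continuous covariate. Derive it from the onset date already needed for inclusion criterion (1).
- Carry the same covariate into the model for the 3-, 6- and 12-month visits.
- Fix both in writing before any outcome data are compared by group, since the trial is already recruiting.
- In Hypotheses and in the planned conclusion, describe the intervention as training started within 1 month of stroke.

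A treatment-by-days estimate and a by-arm report of how much training fell within the month are optional. The trial was sized for a main effect, so an interaction estimate would be imprecise.

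The cost is one extra model term, one derived variable from data already held, and a slightly narrower claim. Recruitment, visits, sample size and treatment are unaffected.
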